## Abstract

**Background:**

Repeat infection with *Chlamydia trachomatis* is common and increases the risk of sequelae in women and HIV seroconversion in men who have sex with men (MSM). Despite guidelines recommending chlamydia retesting three months after treatment, retesting rates are low. We are conducting the first randomised controlled trial to assess the effectiveness of home collection combined with short message service (SMS) reminders on chlamydia retesting and reinfection rates in three risk groups.

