**Discussion:**

This study will provide evidence about the effectiveness of home-collection combined with SMS reminders on chlamydia retesting, repeat infection and reinfection rates in three risk groups. The trial will determine client acceptability and cost effectiveness of this strategy.

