### Cost effectiveness

There is limited evidence regarding the cost effectiveness of home-based versus clinic based rescreening for sexually transmitted infections. A study by Xu et al. found home-collection to be less costly than clinic-based rescreening at $54 per self-collected test versus $118 per clinic-based test [33].

We describe here a randomised controlled trial that aims to assess the effectiveness of home-collection combined with SMS reminders on chlamydia retesting rates in MSM, women and heterosexual men. The trial will also determine client acceptability and cost effectiveness of the approach.

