### Research objectives

The primary objective of the trial is to compare the retest rate 1-4 months after treatment for chlamydia among participants in the home group (3-month SMS reminder and home-collection) compared with the clinic group (3-month SMS reminder to return to the clinic). The secondary objectives are to: compare the chlamydia repeat positive test rate in participants in the home group compared with the clinic group; assess the reinfection rate among participants who retested; determine the acceptability of home-based testing with SMS reminders; and compare health provider costs of home-based specimen collection with routine (clinic based) retesting.

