### Intervention (home testing) arm

The home-collection kit will contain the collection device, illustrated collection instructions, laboratory request form and pre-paid envelope. The collection devices will vary according to the patient’s risk group as follows: for heterosexual men the collection device will consist of a sponge-based urine collection device (UriSWAB®, Copan Diagnostics, CA, USA); for women the collection device will consist of a swab for lower vaginal self-collection and for MSM two collection devices will be provided: (i) a swab for rectal self-collection; and (ii) a UriSWAB for first-pass urine collection.

The swabs and request form will be pre-labelled with identifying information. Three months after chlamydia diagnosis, the clinic will send an SMS reminder to encourage the patient to either: (i) return to the clinic for retesting; or (ii) collect a sample/s using the collection kit and mail it to the lab with the request slip. A purpose-built database will be used to generate a list of patients due to be mailed home-collection kits. The collection kit will be mailed to the patient in an unmarked envelope by the research team. Patients will be instructed in a covering letter to collect their specimen/s and package them according to the instructions provided and mail them to the laboratory in the pre-paid envelope.

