### Control (standard care) arm

Three months after chlamydia diagnosis patients will be sent an SMS reminder by the clinic to encourage them to return to the clinic for retesting. This is routine practice at the two participating clinics.

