### Analysis

#### Chlamydia retesting and repeat positive test rates

The final analysis of primary and secondary outcomes will be performed at the conclusion of the trial. Patient baseline characteristics will be compared by randomised group as appropriate but no formal statistical tests will be undertaken. Analyses will be conducted using STATA statistical analysis software. An intention-to-treat approach will be taken.

In the initial analysis, the percentage of individuals who returned will be cross tabulated by randomised group. The analysis will determine the effect of the intervention on primary and secondary outcomes overall and between risk groups (MSM, women and heterosexual men). The primary analysis will be retesting rates between 1-4 months after a chlamydia diagnosis. Per protocol analyses will include: i) among the home-testing arm: the percentage who retested at home compared with the clinic, and the median time to retest among those who tested at the clinic versus home; ii) in each arm: the median time to retest (overall and in those who retested positive); and iii) factors associated with repeat positivity among those who retested at 1-4 months.

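### The abstract and the analysis section promise an effect on reinfection rates, but the design can show only how many repeat infections and reinfections are detected

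*Protocol article*

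**What the plan says.** All references are to the protocol article.

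The broad claim appears in three places:
- Abstract, Background: the trial is to "assess the effectiveness of home collection combined with short message service (SMS) reminders on chlamydia retesting and reinfection rates in three risk groups".
- Abstract, Discussion: it will provide "evidence about the effectiveness of home-collection combined with SMS reminders on chlamydia retesting, repeat infection and reinfection rates in three risk groups".
- Analysis, Chlamydia retesting and repeat positive test rates: "The analysis will determine the effect of the intervention on primary and secondary outcomes overall and between risk groups". The Outcomes section lists reinfection rate as the second of four secondary outcomes.

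A narrower aim appears elsewhere:
- The end of the Background (Cost effectiveness) says the trial "aims to assess the effectiveness of home-collection combined with SMS reminders on chlamydia retesting rates in MSM, women and heterosexual men". Reinfection is not mentioned.
- Research objectives: repeat positivity is to be compared between the groups, but for reinfection the objective is only to "assess the reinfection rate among participants who retested".
- The main Discussion speaks of raising retesting and detecting repeat positive tests.

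On what the arms receive, the home arm section reads "Three months after chlamydia diagnosis, the clinic will send an SMS reminder to encourage the patient to either" return to the clinic or use the kit. The control arm section reads "Three months after chlamydia diagnosis patients will be sent an SMS reminder by the clinic to encourage them to return to the clinic for retesting".

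**The concern.** Effectiveness on reinfection rates reads as a claim that the strategy changes how many people are reinfected. Retesting could do that by finding an infection, treating it and interrupting transmission. That chain starts after the retest, whereas the outcome is read from the retest itself. This is a matter of time order and would remain if every randomised patient were tested.

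The risk is in the conclusion. A difference between arms in counted reinfections could be reported as the strategy lowering or raising reinfection when it arises from testing. The Background section on chlamydia retesting shows that this is a realistic misreading. Among earlier interventions that reported repeat positivity, all but one had a lower rate in the intervention arm, and the authors suggest that a different mix of people retesting may be part of the reason.

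**Working it through.** **Step 1. What differs between arms, and when.** Both arms get an SMS at three months. The home arm also gets a mailed collection kit at about that time, and its specimens go to a specialist laboratory instead of the clinic's usual provider (Chlamydia testing). Using the kit is the retest. The primary window is 1-4 months after diagnosis, so a retest before month 3 precedes the reminder.

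**Step 2. What is counted.** The Reinfection rate section classifies the repeat positive as reinfection, treatment failure or persistent infection, using genotype, treatment and reported sexual behaviour. Any reinfection so counted was acquired before the specimen was taken.

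**Step 3. What follows the retest.** An online survey is prompted at 4.5 and 5 months. It informs the classification and traces tests done elsewhere. No specimen is scheduled after the retest and no outcome is defined there. Under Clinical and sexual behaviour data, chlamydia results are extracted for all episodes of care in the trial period, so some later routine tests may be on record, but no stated outcome is tied to them.

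**Step 4. The plan's own figures.** Two-sided alpha of 0.05 is an assumption, as the article does not state it; pooled variance, 1:1, no continuity correction.
- 60% versus 40%: n per arm = [1.960 × √(2 × 0.5 × 0.5) + 0.842 × √(0.24 + 0.24)]² / 0.20² = 96.9, so 97 per arm and 194 per risk group, as stated.
- 52% versus 40% with 300 per arm: power 84.0%, consistent with at least 80%.
- 10% versus 23% repeat positivity among expected retesters, 0.40 × 300 = 120 and 0.52 × 300 = 156: power 82.1%. Power of 80% is reached at about 22.6%, which rounds to the stated 23%.

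The figures reproduce. The last one looks for an increase, which fits finding more cases and not preventing them.

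**Step 5. Cases per person randomised with no effect on reinfection.** Let r be the true positivity among retesters, equal in both arms. Cases found per 300 randomised are 120r (clinic) and 156r (home):

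| r | Clinic | Home |
|---|---|---|
| 10% | 12.0 | 15.6 |
| 18% | 21.6 | 28.1 |
| 23% | 27.6 | 35.9 |

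The ratio is 156/120 = 1.3 whatever r is. It is the same for reinfections if they form the same share of repeat positives in both arms. The 10% and 23% come from the sample size section, and 18% is the 3-month rate in the Australian cohort cited in the Background.

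**Step 6. Rate among retesters with no effect on reinfection.** Without selection the difference is zero. For selection, take the symptom mix of the postcard reminder study cited in the Background: 50% of intervention retesters and 23% of control retesters were asymptomatic, so 50% and 77% had symptoms. Positivity by symptom status is assumed, not given in the article.
- 20% with symptoms, 10% without: home 0.50 × 20% + 0.50 × 10% = 15.0%; clinic 0.77 × 20% + 0.23 × 10% = 17.7%.
- 30% and 10%: home 20.0%; clinic 25.4%.

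With no true effect, the home arm looks worse per person randomised and better among retesters.

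**The case against.** The strongest reply is that the abstract is shorthand and that the body is already narrow. The stated aim covers retesting only, the reinfection objective is not comparative, and the Reinfection rate section sets out a classification without an arm comparison. The sentence on primary and secondary outcomes is a blanket one: acceptability is also a secondary outcome, yet it is analysed within the home group. The authors are aware that who retests affects positivity, and they put this tentatively. All of that stands. It shows that the article conflicts with itself and that the broad wording is the outlier. It does not remove that wording from the abstract or the analysis section.

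A reader might go further and infer that nothing is tested afterwards, so the intervention cannot have changed the reinfections counted. The article does not support that. Routine records may hold later tests. Patients also learn their group once they have consented, so a change in behaviour before the retest is not excluded, although the article proposes no such mechanism.

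A reader might also infer that reinfection should be dropped from arm comparisons altogether. That would discard a valid intention-to-treat quantity, namely cases detected per person randomised. It would also be inconsistent, since the same time-order argument applies to repeat positivity, which the plan does compare. Nor does the article anywhere say that it expects to show a reduction.

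**Conclusion.** The concern holds as a claim that the design does not support. The abstract, and the analysis section read with the Outcomes section, promise an effect on reinfection. The trial can show an effect on retesting and on the detection of repeat infection and reinfection.

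The expected effect of the kit on infections present at the retest is about nil. This assumes that knowing the allocation does not change behaviour beforehand and that the outcome is the retest and not a later routine test. Against that near-nil effect, detection alone gives a ratio of 1.3 per person randomised at the planned retest rates. The assumed selection examples give 2.7 to 5.4 percentage points in the opposite direction among retesters (17.7 − 15.0 and 25.4 − 20.0). These are illustrations and not predictions.

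The primary outcome, the sample size and the conduct of the trial are unaffected. What changes is what the trial may conclude about reinfection.

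**What to change.** - In both places in the abstract, replace effectiveness on repeat infection and reinfection rates with effectiveness on retesting and on detection of repeat infection and reinfection.
- In the analysis section, make any arm comparison of repeat positivity or reinfection a comparison of detected cases per person randomised, and label it detection.
- Report the rate among retesters, and the split into reinfection, treatment failure and persistent infection, descriptively.
- State that the trial cannot show whether the strategy reduces reinfection.

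The cost is a narrower headline claim. No extra data are needed. The power statement for repeat positivity is on retesters, so it would have to be restated for the new denominator: the stated 10% and 23% become 0.40 × 10% = 4.0% and 0.52 × 23% = 12.0% of those randomised.

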**Methods/Design:**

The REACT (retest after *Chlamydia trachomatis*) trial involves 600 patients diagnosed with chlamydia: 200 MSM, 200 women and 200 heterosexual men recruited from two Australian sexual health clinics where SMS reminders for retesting are routine practice. Participants will be randomised to the home group (3-month SMS reminder and home-collection) or the clinic group (3-month SMS reminder to return to the clinic). Participants in the home group will be given the choice of attending the clinic if they prefer. The mailed home-collection kit includes a self-collected vaginal swab (women), UriSWAB (Copan) for urine collection (heterosexual men), and UriSWAB plus rectal swab (MSM). The primary outcome is the retest rate at 1-4 months after a chlamydia diagnosis, and the secondary outcomes are: the repeat positive test rate; the reinfection rate; the acceptability of home testing with SMS reminders; and the cost effectiveness of home testing. Sexual behaviour data collected via an online survey at 4-5 months, and genotyping of repeat infections, will be used to discriminate reinfections from treatment failures. The trial will be conducted over two years. An intention to treat analysis will be conducted.

**Discussion:**

This study will provide evidence about the effectiveness of home-collection combined with SMS reminders on chlamydia retesting, repeat infection and reinfection rates in three risk groups. The trial will determine client acceptability and cost effectiveness of this strategy.

**Trial registration:**

Australian and New Zealand Clinical Trials Registry ACTRN12611000968976.

## Background

*Chlamydia trachomatis* is the most frequently reported sexually transmitted infection in most developed countries and notification rates are increasing steadily each year [1-3]. In many countries, the greatest burden of infection is among young heterosexual men and women aged 15-24 years, with population-based prevalence estimates ranging from 3 to 6% [4-7]. High prevalence rates have also been reported in men who have sex with men (MSM), ranging from 5 to 9% for rectal infections and 3 to 6% for urethral infections [8-11].

### Repeat chlamydial infections

Repeat chlamydial infections following treatment are also common. In a prospective cohort of 16-24 year old women attending general practices in the United Kingdom, a repeat infection rate of 29.9% per year following treatment was reported (95% confidence interval [CI]: 19.7-45.4%) [12]. An Australian cohort of 1116 women aged 16-25 years reported a repeat infection rate of 18% at 3 months (95% CI: 8-34%) and 22.3% by 12 months (95% CI: 13.2, 37.6) following treatment [13]. In a review of eight studies, it was reported that 10.9% of heterosexual of men with active follow-up had a repeat infection at 4 months [14]. Higher rates of repeat infection after treatment have been reported in MSM [15]. Repeat chlamydial infections increase the risk of chlamydia-related sequelae such as pelvic inflammatory disease and infertility, when compared to initial infection [16], and in MSM, repeat rectal chlamydia or gonorrhoea infections have been associated with an increased risk of HIV seroconversion [17].

Repeat positive chlamydia tests may result from reinfection from the same partner, an infection from a new partner, inadequate treatment or treatment failure [18]. Batteiger et al. found that of the repeat positive tests among young women participating in a longitudinal cohort, 84.2% were definite, probable, or possible reinfections (different genotypes +/- unprotected sex); 13.7% were probable or possible treatment failures; and 2.2% persisted without documented treatment [18]. This study and others [19,20], have demonstrated that treatment failure with azithromycin may be a contributing factor in repeat positive chlamydia tests, and this has been the subject of recent debate [21,22].

### Chlamydia retesting

Retesting at 3 months is important to prevent onward transmission and sequelae associated with repeat infections. Given that the majority of repeat infections are the result of existing partners not being treated, repeat positivity is also an important indicator of the effectiveness of partner notification.

Although clinical guidelines in a number of countries recommend retesting after treatment for chlamydia [23-27], retesting rates are low, especially amongst men. In a recent analysis of 2008-2010 United States (US) laboratory data, chlamydia retesting rates within a year among men and non-pregnant women, were 22% and 38% respectively [28]. In a 5-year period between 2004 and 2008, the proportion of Australian sexual health service patients with chlamydia infection who were retested in 30-120 days was 8.6% in MSM, 11.9% in heterosexual males and 17.8% in heterosexual females [29]. In England, retesting rates within a year among 15 to 24 year olds in 2010 ranged from 18.4% in the National Chlamydia Screening Program dataset to 26.1% in the genitourinary medicine clinic activity dataset [30].

The true clinical impact of increased rescreening has not yet been established. Of the interventions aiming to increase retesting conducted to date, few measured repeat positive tests and none discriminated between reinfections and treatment failures [31-37]. Among the interventions which did report repeat positive test rates, despite higher retesting rates, the rate of repeat infection in all but one study, was lower in the intervention arm compared with the control arm. However only one study showed this difference was statistically different.

Based on the study by Batteiger et al. [18], the majority of repeat positive tests would be expected to be reinfections, which suggests that rescreening strategies may be reaching more asymptomatic patients and those at lower risk of reinfection. For example, in the postcard reminder study by Paneth-Pollack et al. [32], 50% of retesters in the intervention arm were asymptomatic compared to 23% in the control group. People with symptoms may be more likely to initiate retesting, and this may help to account for the lower rates of repeat infection found, despite higher retesting rates. This highlights the importance of measuring both retesting and repeat positive test rates in studies which aim to increase retesting.

The high sensitivity of nucleic acid amplification tests (NAAT) has enabled the use of self-collected specimens, such as urine and vaginal swabs, for the diagnosis and screening of chlamydia and gonococcal infections [38]. Self-collected urine, vaginal and rectal specimens have been widely used in a variety of clinical and non-clinical settings to increase access to chlamydia screening and rescreening [37,39-42] and have been found to be acceptable in men and women [43-46]. A previous study in Australia has confirmed the robustness of swabs when transported for up to a week through routine postal systems [47].

### Interventions to increase chlamydia retesting

Mailed home collection kits have been demonstrated in a meta-analysis of controlled studies by Guy and colleagues, to increase retesting rates by an average of 30% (pooled effect estimate = 1.30; 95% CI: 1.10-1.50) [48]. The same meta-analysis showed reminder strategies including phone calls (+/- letters) and postcard reminders also resulted in a modest increase in rescreening.

A reminder strategy that was not used in the studies reviewed by Guy et al. was the use of short message services (SMS) reminders. SMS and telephone reminders have been found to be effective for a variety of health related purposes such as reducing missed appointments [49] and increasing vaccination uptake [50], with SMS reminders shown to be more cost-effective [49,51]. SMS reminders have the advantage of automation, convenience, confidentiality and immediacy [52] and have been found to be acceptable in the sexual health context [53,54]. Subsequent to the review by Guy et al. [48], three Australian before-after studies have demonstrated that SMS reminders increase STI retesting rates in sexual health clinic patients [35,52,55].

### Cost effectiveness

There is limited evidence regarding the cost effectiveness of home-based versus clinic based rescreening for sexually transmitted infections. A study by Xu et al. found home-collection to be less costly than clinic-based rescreening at $54 per self-collected test versus $118 per clinic-based test [33].

We describe here a randomised controlled trial that aims to assess the effectiveness of home-collection combined with SMS reminders on chlamydia retesting rates in MSM, women and heterosexual men. The trial will also determine client acceptability and cost effectiveness of the approach.

## Methods/Design

### Study design/setting

This is a non-blinded, randomised controlled trial (RCT) where individuals are randomised in a 1:1 ratio to an SMS reminder and home-based, self-collected samples (home group) or an SMS reminder and clinic testing (clinic group). The trial is being conducted in two Australian sexual health clinics (Melbourne and Sydney Sexual Health Centres). The study is diagrammatically represented in Figure 1.

**Figure 1 F1:**
[figure not shown]
Schematic of REACT study design.

### Research objectives

The primary objective of the trial is to compare the retest rate 1-4 months after treatment for chlamydia among participants in the home group (3-month SMS reminder and home-collection) compared with the clinic group (3-month SMS reminder to return to the clinic). The secondary objectives are to: compare the chlamydia repeat positive test rate in participants in the home group compared with the clinic group; assess the reinfection rate among participants who retested; determine the acceptability of home-based testing with SMS reminders; and compare health provider costs of home-based specimen collection with routine (clinic based) retesting.

